# Effectiveness of Gyejibongnyeong-Hwan for shoulder pain: study protocol for a randomised, wait-list controlled pilot trial

**DOI:** 10.1186/s13063-020-4092-y

**Published:** 2020-02-17

**Keywords:** Gyejibongnyeong-Hwan, Gui-Zhi-Fu-Ling-Wan, Keishibukuryogan, Shoulder pain, Hyperlipidaemia, Blood stasis

## Abstract

**Background:**

Shoulder pain is an uncomfortable feeling in the muscle around the shoulder. The cause of myalgia is the accumulation of lactic acid in muscles and impaired blood circulation, which is called blood stasis in traditional East Asian medicine. This study aimed to explore the therapeutic effect of Gyejibongnyeong-Hwan (GBH) for shoulder discomfort related to blood stasis before and after treatment.

**Methods/design:**

This study will be a double-centre, randomised, wait-list controlled pilot trial. Participants with shoulder pain and with a visual analogue scale score of 4 or higher out of 10, blood stasis score of 9 or higher, and triglyceride level of ≥150 mg/dl or total cholesterol level of ≥200 mg/dl will be recruited from two university hospitals. A total of 40 participants will be assigned to the immediate and waiting treatment groups. The immediate treatment group will receive GBH for 8 weeks on enrolment while the waiting treatment group will receive GBH for 8–16 weeks after 8 weeks of controlled waiting. The primary outcome is shoulder pain, and the secondary outcomes are the blood stasis score, blood pressure, ankle–brachial pressure index, brachial–ankle pulse wave velocity, body mass index, waist circumference, indexes of oximetry, and levels of blood lipid, blood sugar, resistin, C-reactive protein, serum amyloid P, and D-dimer.

**Discussion:**

The results of this pilot trial will be the bases for a full-scale clinical trial of GBH.

**Trial registration:**

Clinical Research Information Service, KCT0003837. Registered on 23 April 2019. https://cris.nih.go.kr/cris/en/search/search_result_st01.jsp?seq=14258

## Background

Shoulder pain is a feeling of stiffness or discomfort around the shoulder joint, especially in the trapezius muscle. The incidence of shoulder pain in primary care is 14.7 per 1000 patients per year, and approximately 70% of the population experiences more than one episode in a lifetime [1–3]. Electrotherapy (transcutaneous electrical nerve stimulation, TENS), ultraviolet therapy, hot pack, massage, and sodium channel blocker drugs are used to alleviate muscle contractions; however, these interventions are largely ineffective [4, 5]. The tension in the shoulder muscles worsens with prolonged sitting at a computer and improper posture, and under physical and emotional stress. Myalgia is caused by the accumulation of lactic acid in the muscles and impaired blood circulation. In traditional East Asian medicine, muscle cramps and chronic musculoskeletal pain are considered to be due to blood stasis and can lead to limitations in shoulder movements by blocking the meridians [6].

Blood stasis is defined as the pathological stagnation of blood in certain parts of the body. It manifests as a variety of symptoms, including pain in a fixed location, a dark-purple appearance of the face or tongue, bleeding, blood spots under the skin, and an astringent pulse [7]. It is believed that blood stasis causes lipoprotein disorders such as thrombosis and the formation of atheromatous plaques [8–10]. Several herbal formulae that reduce blood stasis are helpful in the management of metabolic disorders [11]. Furthermore, blood stasis can occur after physical injuries, and the use of herbal medicine to eliminate blood stasis has been reported to alleviate muscle pain in some cases [12].

Therefore, we hypothesised that Gyejibongnyeong-Hwan (GBH), a herbal formula for dissipating blood stasis, is effective for the treatment of shoulder pain and hyperlipidaemia. GBH was approved as a medicine for shoulder discomfort by the Ministry of Food and Drug Safety (MFDS), South Korea [13]. In previous studies, GBH has been reported to ameliorate metabolic diseases such as hyperglycaemia and hyperlipidaemia [14, 15]. The primary objective of this pilot trial is to explore whether GBH relieves shoulder pain related to blood stasis. The secondary objective is to determine whether GBH is also helpful in improving blood lipid levels associated with blood stasis.

## Methods

### Study design

This is a multi-centre, randomised, wait-list controlled pilot study. This study will determine the effectiveness of GBH by comparing two groups: the immediate GBH treatment group and the waiting treatment group. Furthermore, the findings before and after GBH treatment will be compared in each group. The immediate treatment group will undergo an 8-week treatment period and an 8-week follow-up period. The waiting treatment group will undergo an 8-week waiting period and an 8-week treatment period. An overview of the trial process is shown in Fig. 1.

**Fig 1 Fig1:**
[figure not shown]
Flow chart of the trial process. GBH Gyejibongnyeong-Hwan

### Setting

This trial will be conducted at two hospitals: Chungju Oriental Hospital of Semyung University and Jecheon Oriental Hospital of Semyung University. This study was sponsored by Korea Institute of Oriental Medicine (KIOM), and KIOM wrote the protocol following the Standard Protocol Items: Recommendations for Interventional Trials (SPIRIT) checklist (Additional file 1). Both centres will be managed by KIOM during the study period.

### Recruitment

Patients with shoulder pain and blood stasis will be recruited over 6 months at Chungju Oriental Hospital of Semyung University and Jecheon Oriental Hospital of Semyung University. Posters will be posted publicly inside and outside both hospitals. Anyone interested in the study can contact the clinical research coordinator (CRC) of each site via telephone or e-mail. Then, a Korean medical doctor will screen participants for eligibility. Those who agree to participate in the study and provide written informed consent will be enrolled.

### Inclusion and exclusion criteria

The following participants will be included in this trial: those having physical strength, cold feet, and shoulder pain and a visual analogue scale (VAS) score of 4 or higher out of 10; those with a blood stasis score of 9 or higher (15-item questionnaire for diagnosis of blood stasis with metabolic diseases) (Appendix: Table 2); triglyceride (TG) level of ≥150 mg/dl or total cholesterol (TC) level of ≥200 mg/dl; and those who voluntarily agree to participate in this study and will comply with the restriction during the study period.

The following patients were excluded: those who are unable to give informed consent by themselves; pregnant women (for women of child-bearing age, the human chorionic gonadotropin (HCG) level will also be measured before GBH administration); those participating in another clinical trial; and those receiving medicines for therapeutic purposes.

### Randomisation, allocation, and blinding

Participants meeting the inclusion and exclusion criteria will be randomly allocated to either the immediate treatment group or the waiting treatment group at a ratio of 1:1. A computer-generated randomisation schedule based on a table of random digits will be used for group assignment. Access to the sequence will be restricted to the KIOM data manager (who is independent of the study team). The randomisation sequence will be included in a password-protected computer file and allocated to each hospital by an investigator.

Since this is an open-label trial without placebo, neither researchers nor participants will be blinded.

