#### Secondary outcomes

The secondary outcomes include the blood stasis score, the high-density lipoprotein cholesterol (HDL-C), low-density lipoprotein cholesterol (LDL-C), TG, TC, fasting blood glucose (FBG), resistin, C-reactive protein (CRP), serum amyloid P (SAP), and D-dimer levels, ABI, baPWV, BP, BMI, WC, and the seven oximetry indices (SpO_2_, SpHb, PVI, SpOC, PR, SpMet, and PI). Blood stasis scores, ABI, baPWV, oximetry indexes, and levels of resistin, CRP, SAP, and D-dimer will be used to evaluate blood stasis. CRP, as an inflammation marker, will be also used as an outcome of trapezius myalgia treatment [16]. HDL-C, LDL-C, TG, TC, and FBG levels, BP, BMI, and WC will be measured to verify the effectiveness of GBH for treating metabolic diseases referred to in previous studies.

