## Discussion

The aim of this study, as a pilot trial, is to observe the clinical effectiveness of GBH. The study treatment GBH (known as Gyejibongnyeong-Hwan in Korean medicine, Gui-Zhi-Fu-Ling-Wan in traditional Chinese medicine, and Keishibukuryogan in Kampo medicine) is a herbal medicine used to eliminate blood stasis. It consists of five herbs (Cinnamomi ramulus, *W. extensa*, *P. suffruticosa* Andrews, *P. persica*, and *P. lactiflora*) [17, 18]. GBH has been used mainly for treating primary dysmenorrhoea, uterine myoma [19], and climacteric symptoms such as hot flashes [18]. A phase II trial to assess the efficacy of GBH (TU-025) Tsumura & Co (Tokyo, Japan) for hot flash management was conducted in the United States; however, the results did not show significant clinical effectiveness. GBH has also been reported to be effective in the management of metabolic diseases [14]. In South Korea, GBH is one of the most popular herbal medicines for blood stasis management and has been approved as a treatment for shoulder discomfort by the MFDS [13]. Since GBH has not yet been approved for hyperlipidaemia, indices related to blood lipids will be determined as secondary outcomes. Our research team has plans for further clinical trials for Investigational New Drug application, depending on the results of this pilot trial.

The outcomes used to evaluate blood stasis were also designated as study variables for this pilot trial. A blood stasis questionnaire was developed by KIOM, the results of which will be evaluated based on standard guidelines by Korean medical doctors [20]. A questionnaire for blood stasis with metabolic diseases was developed and published recently [21]. This is an abbreviated version of the original questionnaire; the new questionnaire comprises 15 questions (from the original 31 questions) related to metabolic diseases. The 15-item questionnaire will be used at screening, and after registration, blood stasis will be evaluated using the original questionnaire (Appendix: Table 3). Outcomes associated with oximeter measurements and some biomarkers (i.e., resistin, CRP, SAP, and D-dimer) have been used in previous blood stasis studies and will also be measured in this pilot trial to determine whether they are associated with blood stasis. The ABI and baPWV indicate narrowing and stiffening of arteries and are therefore expected to be appropriate for the evaluation of blood stasis [22].

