There are some limitations to this pilot study. First, this is an open-label, wait-list controlled trial in which neither the participants nor the clinical practitioners will be blinded. We could have designed a randomised controlled trial using a placebo; however, we decided to administer GBH to both groups. Since the sample size is relatively small, we adopted a wait-list controlled design that would allow the evaluation of GBH effectiveness, without reducing the number of participants receiving GBH. Second, the outcome measures for shoulder pain are only the VAS score and the CRP level, and these may not be enough. However, this study has been designed to minimise the burden of participants and the number of patient-reported outcomes. Furthermore, the blood stasis questionnaire contains pain-related items; therefore, other measurements for shoulder pain were not included in this study, such as the Shoulder Pain and Disability Index (SPADI) and the Disabilities of the Arm, Shoulder and Hand (DASH) questionnaire [23]. Third, a follow-up investigation will not be performed in the waiting group, due to the length of the entire study period and research funds. Fourth, the VAS score, which is the primary outcome, is self-reported, and there may be a measurement bias. Nonetheless, this study is meaningful because the findings of this study will serve as a reference for designing the full-scale randomised controlled trial.

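### The lack of a placebo does not justify leaving the analyst and the doctor who rates blood stasis signs unblinded

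*Protocol article*

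**What the plan says.** The section on randomisation, allocation and blinding gives the rule and its reason in one sentence: "Since this is an open-label trial without placebo, neither researchers nor participants will be blinded". The first limitation in the Discussion repeats it: "this is an open-label, wait-list controlled trial in which neither the participants nor the clinical practitioners will be blinded".

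The Secondary outcomes section begins: "The secondary outcomes include the blood stasis score". On the blood stasis questionnaire, the Discussion says: "the results of which will be evaluated based on standard guidelines by Korean medical doctors". It also fixes the instrument: "after registration, blood stasis will be evaluated using the original questionnaire". That is the 31-item form, printed in the Appendix as Table 2 (the Discussion cites it as Table 3).

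The only outcome for which the limitations name measurement bias is the VAS: "the VAS score, which is the primary outcome, is self-reported, and there may be a measurement bias".

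On the allocation list, the article says: "Access to the sequence will be restricted to the KIOM data manager (who is independent of the study team").

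The Statistical analyses section names a t test or a rank-sum test, chosen after a normality test, for changes in scores. It also names ANCOVA adjusted for baseline for the outcome variables.

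**The concern.** The reason is narrower than the rule. Without a placebo, participants know whether they are taking GBH, and so do those who give it. A person who grades tongue colour, or who runs the week-8 comparison, need not know.

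Two things are at stake. First, a doctor who knows that one group has had a remedy for blood stasis and the other has not may grade colour, tenderness or skin signs more favourably in the treated group. That would move the between-group difference towards GBH. Second, the article leaves more than one test open for the same outcomes. If the analyst can see which group is which, the choice among them can be influenced by the result.

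The Discussion says that the pilot will inform a full-scale trial and further clinical trials, so a biased estimate would carry forward.

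**Working it through.** No figure in the plan tests this point, so the check sets the passages side by side, counts items and adds one calculation for scale.

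**Whom the stated reason covers**

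- Participants: covered, since they know whether they take GBH.
- Those who give GBH: covered.
- Doctors rating blood stasis: covered only if they also treat or dispense. The article does not say whether they do. The Recruitment section mentions one Korean medical doctor who screens; the number and roles of doctors at each site are not given.
- Analyst: not covered. The article does not say who analyses. A data manager independent of the study team already holds the sequence, so coded labels are practicable.

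**How much of the score is examiner-judged (31-item form, Appendix)**

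- Items 3–10 (mouth, tongue, lips, face): 8
- Items 13, 14, 16, 17 (abdominal tenderness and resistance): 4
- Items 25–28 (skin signs): 4
- Item 31 (pulse): 1

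Total 8 + 4 + 4 + 1 = 17, and 17/31 = 55%. The other 14 are wholly or partly reported by the patient. The split is a judgement from item wording. The four tenderness items also depend in part on the patient's response.

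**Whether the schedule lets a rater be masked**

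By the Data collection section, at week 8 the immediate group is at visit 3, having also been assessed at visit 2. The waiting group is at visit 1 after its wait. Compliance, adverse events and satisfaction are collected at visit 3. Visit labels and these data would therefore identify the group, and so might the attendance pattern. The same holds for the analysis file: only the immediate group has a week-4 value that could be carried forward to week 8.

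**Scale, under assumed shifts**

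Inputs from the article: two-sided 0.05; 40 participants at 1:1, so 20 per group; 25% drop-out, so 20 × 0.75 = 15 per group. Assumed: a rating shift of b SD in the group difference, no true effect, and a normal approximation.

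s = b / √(2/n); error rate = 1 − Φ(1.96 − s) + Φ(−1.96 − s)

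Example with n = 20 and b = 0.3: √(2/20) = 0.316, s = 0.949, error rate = 0.158.

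| b (SD, assumed) | 20 per group | 15 per group |
|---|---|---|
| 0 | 0.050 | 0.050 |
| 0.1 | 0.062 | 0.059 |
| 0.2 | 0.097 | 0.085 |
| 0.3 | 0.158 | 0.130 |
| 0.5 | 0.353 | 0.278 |

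This shows how sensitive the comparison would be to a shift of a given size. It does not estimate the shift.

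**The case against.** Four objections deserve weight.

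- **Disclosure.** The first limitation says that "neither the participants nor the clinical practitioners will be blinded", and practitioners may well include the rating doctors. This stands in part: the lack of blinding is disclosed, but its consequence for a doctor-rated score is not.
- **Condensation.** An article commonly leaves analyst masking and sample coding to the full protocol. This stands for the laboratory, which is not mentioned; nothing says that samples are uncoded. It is weaker for rater and analyst, because the article states a rule for researchers without exception and gives a reason that does not reach them.
- **Weak masking.** Attendance pattern or the participants themselves may reveal the group. This stands, and makes rater masking a partial remedy.
- **Scope.** The score is one of 22 listed secondary outcomes, and the primary outcome is untouched. This stands.

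A reader might also infer more than the article supports:

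- *That every form of blinding has been dropped.* The text names researchers, participants and clinical practitioners, and no others.
- *That a masked rater needs no extra staff.* Numbers and roles of doctors are not given, and the people described as independent are a data manager and monitoring staff, not raters.
- *That the bias is about 0.3–0.8 SD.* This would follow from moving all 16 graded examiner-judged items by 0.25–0.5 category (16 × 0.25 = 4 to 16 × 0.5 = 8 points) and dividing by an SD of 10–15. The shift, the SD and the summed scoring are all assumed. Entry needs only 9 points on the 15-item form, which three 3-point items supply, so many signs may be rated as absent and could not be graded lower under GBH.
- *That a masked rater would make the questionnaire an independent check on the VAS.* The Discussion cites its pain items as a reason to omit other shoulder measures, but those items are mainly symptoms reported by unblinded patients and lie outside the 17.

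**Conclusion.** The point holds in a limited form. The stated reason justifies unblinded participants and treating staff. It does not justify an unblinded analyst, or an unblinded rater of the roughly 17 examiner-judged items.

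The size of any bias cannot be derived from the article; the error rates above depend wholly on the assumed shift. The case for coded analysis needs no such figure, because it rests on the choice of tests left open and on an independent data manager already being in place. The case for a masked rater depends on site staffing that is not described, and its protection would be incomplete.

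Neither measure protects the self-reported VAS or the patient-reported questionnaire items. Nor does either protect the waiting group's before–after comparison, which has no concurrent untreated group.

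**What to change.** Replace the blinding sentence with text to this effect:

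*Participants and treating doctors are not blinded. The independent data manager prepares a baseline and week-8 data set with groups labelled A and B, missing values already carried forward, and no visit numbers, compliance or satisfaction data. The statistician fixes the choice of test and completes the week-8 comparison before the labels are opened.*

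For the rating, where a site already has a study doctor who neither treats nor dispenses, that doctor rates the examiner-judged items without being given group or visit number. Where a site does not, say so, and list unmasked rating of the blood stasis score as a limitation beside the VAS.

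**Cost.** Coded analysis takes a small amount of data-management work. The statistician must also work from the coded file before using the final data sets, to which the article gives the research team access. Masked rating requires compliance, adverse-event and satisfaction questions to be handled by someone else, and some ratings will still be unmasked. The Trial status section reports five participants enrolled and none completed as of July 2019, so at that point no week-8 comparison could yet have been run on completed participants.

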### Intervention

The immediate treatment group will receive GBH for 8 weeks on enrolment, and the waiting treatment group will receive GBH for 8–16 weeks at 8 weeks after enrolment. Every participant will receive 3.0 g of GBH (Hanpoong Pharm & Food Co., Ltd) twice a day for 8 weeks. GBH is a light-brown granular substance consisting of Cinnamomi Ramulus, *Wolfiporia extensa*, *Paeonia suffruticosa* Andrews, *Prunus persica*, and *Paeonia lactiflora* in an equal ratio. Any other medicine or treatment that may affect shoulder pain and hyperlipidaemia will be prohibited during the study period.

### Sample size

This trial is a pilot study that examines the feasibility of conducting a large-scale randomised clinical trial for the use of GBH to treat shoulder pain related to blood stasis. No adequate references could be found with regard to the sample size; hence, a sample size of 40 patients is determined to be adequate considering a 25% drop-out rate. Participants will be assigned to either the immediate treatment group or the waiting treatment group at a ratio of 1:1.

### Data collection

The following demographic data will be collected on the enrolment date: age, sex, occupation, height, weight, alcohol habit, and smoking status. Blood tests and blood stasis questionnaire evaluation will be conducted and VAS scores for shoulder pain will be assessed during the screening visit. After randomisation, the ankle–brachial pressure index (ABI), brachial–ankle pulse wave velocity (baPWV), oxygen saturation (SpO_2_), total haemoglobin (SpHb), pleth variability index (PVI), oxygen content (SpOC), pulse rate (PR), methaemoglobin (SpMet), perfusion index (PI), blood pressure (BP), body mass index (BMI), and waist circumference (WC) will be assessed (visit 1). Blood tests, blood stasis questionnaire evaluation, and VAS score evaluation will be conducted again during visit 1 in the waiting treatment group since the subjects are required to wait for 8 weeks after randomisation. SpO_2_, SpHb, PVI, SpOC, PR, SpMet, and PI will be measured using an oximeter (Masimo Corp.). Blood tests, blood stasis questionnaire evaluation, and oximeter measurements will be performed and shoulder pain, ABI, baPWV, BP, BMI, and WC will be assessed every 4 weeks after GBH has been received (visits 2 and 3). Furthermore, compliance and adverse events will be assessed every 4 weeks (visit 2 and 3), and patient satisfaction will be evaluated after 8 weeks of intervention (visit 3). At the follow-up visit in the immediate treatment group, blood tests, blood stasis questionnaire evaluation, oximeter measurements, assessment of shoulder pain, and determination of ABI, baPWV, BP, BMI, and WC will be performed (visit 4). The time points of the evaluations are presented in Table 1.

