### Statistical analyses

All analyses will be conducted according to the intention-to-treat (ITT) principles. All statistical analyses will be two-sided, and statistical significance will be set at 0.05. The last-observation-carried-forward (LOCF) method will be used to input missing values. An independent *t* test or Wilcoxon rank-sum test will be used to compare changes in scores after performing the Kolmogorov–Smirnov test to confirm the normality of the distribution. All values will be presented as mean and standard deviation values or *n* (%) unless stated otherwise. Outcome variables will be analysed using the corresponding analysis of covariance (ANCOVA) considering the baseline scores as covariates. All statistical analyses will be performed using the SAS statistical package, version 9.4 (SAS Inc., Cary, NC, USA).

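### As the Data collection text reads, 11 of 22 secondary outcomes have only one untreated value in the waiting group, so their planned change-score and baseline-adjusted group comparisons cannot be run

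*Protocol article*

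**What the plan says.** All references are to the protocol article.

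- **Study design.** Effectiveness is to be judged by "comparing two groups: the immediate GBH treatment group and the waiting treatment group". The timeline is: "The waiting treatment group will undergo an 8-week waiting period and an 8-week treatment period". The only period in which one group takes GBH and the other does not is therefore weeks 0 to 8. Before-after comparison within each group is a separate declared aim.
- **Data collection, screening.** Blood tests and the blood stasis questionnaire are done, and "VAS scores for shoulder pain will be assessed during the screening visit". On the enrolment date the demographic data include "age, sex, occupation, height, weight, alcohol habit, and smoking status".
- **Data collection, visit 1.** ABI, baPWV, the seven oximetry indices, and then "blood pressure (BP), body mass index (BMI), and waist circumference (WC) will be assessed (visit 1") come after randomisation. No earlier measurement of them is described. Blood tests, questionnaire and VAS are "conducted again during visit 1 in the waiting treatment group since the subjects are required to wait for 8 weeks after randomisation".
- **Data collection, visits 2 and 3.** These are at 4-week intervals after GBH has started. Visit 4 is a follow-up visit in the immediate group only.
- **Statistical analyses.** Changes are compared by t test or Wilcoxon rank-sum test, and "Outcome variables will be analysed using the corresponding analysis of covariance (ANCOVA) considering the baseline scores as covariates". No outcome is excepted.

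**The concern.** A change score or a baseline-adjusted ANCOVA for GBH versus waiting needs two values per participant: one at about randomisation and one at the end of the control period. For the outcomes that start at visit 1, the text gives the waiting group only one value taken off treatment. The schedule and the analysis as stated do not fit together for these outcomes.

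Two things are at stake. First, an analyst who follows the Statistical analyses section literally may take visit 1 as baseline in both groups. Each group's change from visit 1 to visit 3 is then a change over 8 weeks of GBH, and the randomised control drops out of the comparison. Second, even if the analyst avoids this, the precision that a baseline covariate would give is lost. It cannot be recovered later for anyone whose baseline was not taken. ABI, baPWV and oximetry are among the measures that the Secondary outcomes section assigns to evaluating blood stasis, and the pilot is meant to inform a full-scale trial.

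**Working it through.** **Step 1: timeline.** Inputs are the Study design and Data collection sections. Visits 2 and 3 are 4 and 8 weeks after GBH starts, so visit 1 is the pre-treatment visit in each group. The stated reason for repeat testing, "since the subjects are required to wait for 8 weeks after randomisation", makes sense only if the waiting group's visit 1 follows the wait.

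| Group | Screening | Visit 1 | Visit 2 | Visit 3 | Visit 4 |
|---|---|---|---|---|---|
| Immediate | before week 0 | about week 0, untreated | week 4, on GBH | week 8, on GBH | week 16, follow-up |
| Waiting | before week 0 | week 8, untreated | week 12, on GBH | week 16, on GBH | none |

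For the outcomes that start at visit 1, the waiting group has values at weeks 8, 12 and 16. Only week 8 is untreated, and it is the end-of-control value.

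**Step 2: the alternative reading.** Suppose visit 1 were week 0 in both groups. The waiting group's next stated measurements would be visits 2 and 3, already on GBH, so there would be a baseline but no end-of-wait value. On either reading there is one untreated value, and the change over the control period cannot be computed.

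**Step 3: count.** From the Secondary outcomes section:
- blood stasis score: 1
- HDL-C, LDL-C, TG, TC, FBG, resistin, CRP, serum amyloid P, D-dimer: 9
- ABI, baPWV, BP, BMI, WC: 5
- oximetry indices: 7

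The total is 1 + 9 + 5 + 7 = 22. Those listed first at visit 1 number 5 + 7 = 12. BMI can be derived at enrolment from height and weight in both groups, which leaves 12 − 1 = 11.

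**Step 4: what imputation can do.** Last observation carried forward moves an earlier value forward. In the waiting group nothing precedes visit 1 for these 11 outcomes, so it cannot supply the missing baseline.

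**Step 5: size of the precision loss.** The article gives no effect size, SD or power, so its sample size of 40 cannot be reproduced. With residual SD equal to SD × √(1 − ρ²) under ANCOVA, the variance without the baseline is 1/(1 − ρ²) times the variance with it. The correlation ρ between baseline and week 8 is an assumption.
- ρ = 0.5: 1/(1 − 0.25) = 1.33
- ρ = 0.8: 1/(1 − 0.64) = 2.78

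The detectable difference in SD units (normal approximation, two-sided 0.05, 80% power) is (1.96 + 0.84) × √(1 − ρ²) × √(2/n). If the stated 25% drop-out occurs, 40 × 0.75 = 30, or 15 per arm.

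| n per arm | week-8 values only | ρ = 0.5 | ρ = 0.7 | ρ = 0.8 |
|---|---|---|---|---|
| 15 | 1.02 | 0.89 | 0.73 | 0.61 |
| 20 | 0.89 | 0.77 | 0.63 | 0.53 |

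**The case against.** **The timing is inferred.** No sentence gives a week number for the waiting group's visit 1. Table 1 is not shown, and its legend has marks that apply to one group only, so an extra week-0 measurement cannot be excluded. This stands as a limit on certainty. If Table 1 contains such a measurement, the Data collection text should be brought into line with it.

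**Baseline is not defined in the article, and the full protocol or analysis plan may define it.** This is fair, and the article does not say that visit 1 will be the baseline in both groups. The GBH-versus-GBH comparison is a risk, not a stated plan. But no definition can supply a value that was never measured.

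**A reader might infer that these outcomes have no control at all.** The documents do not support that. On the week-8 reading, immediate visit 3 (on GBH) and waiting visit 1 (untreated) form a concurrent randomised contrast at week 8. What is lost is the change score and the adjustment, not the control. The within-group before-after comparisons also survive.

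**A reader might count all 12 measures, or fear for the main result.** BMI is recoverable. VAS, the primary outcome, is taken at screening and again at the waiting group's visit 1. So are the blood tests, which carry the stated secondary objective on lipids.

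**Conclusion.** The point holds for 11 of the 22 named secondary outcomes: ABI, baPWV, the seven oximetry indices, BP and WC. As the text reads, the change-score and baseline-adjusted ANCOVA comparison of GBH versus waiting cannot be carried out for them. That there is only one untreated waiting-group value holds on either reading of visit 1. That this value falls at week 8, and so allows a randomised week-8 contrast, rests on the stated reason for repeat testing. Both assume that Table 1 adds no further measurement.

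The numerical cost (variance 1.33 to 2.78 times larger) depends wholly on assumed correlations of 0.5 to 0.8 and is an illustration. Severity is moderate: these are secondary outcomes of a pilot, and the primary outcome and the lipid objective keep their randomised comparison.

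**What to change.** **Participants still to be enrolled.** Take ABI, baPWV, oximetry, BP and WC in both groups at screening or randomisation, and repeat them at the waiting group's visit 1, as is already done for VAS and the blood tests. The questionnaire is not a good model for this, because the Discussion uses the 15-item form at screening and the original form after registration. The cost is one extra set of non-invasive measurements in about 20 people, at a visit they already attend. The reach may be small: Trial status expects recruitment to finish by 31 March 2020, and the article was published on 17 February 2020.

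**Participants already enrolled, or if the measurement is not added.** Specify the between-group analysis of these 11 outcomes as week-8 values, immediate visit 3 versus waiting visit 1, without outcome-baseline adjustment. State that the waiting group's visit 1 is its end-of-control value and not its baseline in between-group analyses. In the immediate group visit 1 remains the baseline. For BMI, use the value derived from enrolment height and weight as the covariate in both groups.

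The second part costs only wording. Its limits are the lower precision shown above and the absence of any value for a waiting-group participant who leaves before visit 1. Whichever route is taken, the Data collection text and Table 1 should give the week of visit 1 for each group.
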